### Usual care

In the usual care group, patients will receive routine discharge education at hospital. After they are discharged, they will go to their usual outpatient clinic of the hospital to receive follow-up and outcome measures at 3 and 6 months. They will not be referred to the community health service center. They will be asked to record the number of adverse events and unplanned hospital admissions/use of emergency care services during 3-month and 6-month follow-up in a usual care table (Additional file 5). The researcher will record the HbA1c and lipid levels close to the 3-month and 6-month follow-up from the patients’ medical record.

### Outcome measures

#### Primary outcome

The primary outcome is systolic blood pressure at 6-month follow-up adjusted for baseline value. At each measurement point, blood pressure will be measured three times at 5-min intervals on the participant’s right arm in a sitting position. The average of the three blood pressure readings will be calculated as the final BP reading for each group at each time point, which minimizes measurement error.

#### Secondary outcomes

Secondary outcomes are the following outcomes at 6-month follow-up adjusted for baseline value: (1) hypertension and diabetes-related health knowledge score measured by a combination of the Hypertension Knowledge-Level Scale (HK-LS) [32] and the Diabetes Knowledge Questionnaire (DKQ) [33]; (2) medication adherence and health lifestyle adherence score measured by the Treatment Adherence Questionnaire of Patients with Hypertension (TAQPH) [34]; (3) HbA1c and lipid values; (4) quality of life score measured by the hypertension scale of the Quality of Life Instruments for Chronic Diseases (QLICD-HY) [35]; (5) the incidence of adverse events and complications associated with hypertension, diabetes, treatments and geriatric syndromes recorded by patients/or carers in the “intervention diary—patient version”; and (6) the incidence of unplanned hospital admissions/use of emergency care services due to uncontrolled hypertension, diabetes and geriatric syndromes recorded by patients or carers in the “intervention diary—patient version”.

Through the study, we hope to identify the challenges that patients face in their hypertension management in the community healthcare settings and to evaluate how to overcome these challenges by improving the capacity of the primary care system. Hence, two open-ended questions will be included for patients upon study completion: (1) Are you satisfied with the follow-up provided by the GP and community nurse in the community health service center? (If not, please explain the reason); and (2) Did you encounter any difficulties of care in the community health service center after discharge? (If yes, please list the difficulties you encountered).

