#### Stage 1: interventions at hospital

1.1.Individualized discharge education.Patients will be given two face-to-face individualized health education sessions specific to diabetic patients with hypertension by the in-charge nurse. The health education includes health behavior education, disease-associated education and medication education with 15 min for each session. A geriatrics condition screening will also be undertaken using the widely recognized evidence-based screening tool “Fulmer SPICES Comprehensive Assessment Tool for Older Adults” [31]. Education on preventing and managing geriatric conditions will be provided by the in-charge nurse based on the findings from the screening.1.2.Lifestyle modification goals: intervention diary—patient version.1.2.1.Patients will be asked to establish lifestyle modification goals and develop personal action plans with the in-charge nurse. Patients will be provided an “intervention diary—patient version” (Additional file 2) to document their lifestyle modification goals, personal action plans, progress toward the goals, medication adherence, adverse events and unplanned hospital admissions/use of emergency care services.1.2.2.Patients will be asked to discuss and establish their diet plan with the in-charge nurse. The diet plan will be recorded in the “intervention diary—patient version”.1.3.Individualized medication treatment.Prior to discharge, patients will be given an individualized medication treatment plan by the medical specialist. Individualized medication treatment will be recorded in the “intervention diary—patient version”.1.4.Referral to the community health service center: intervention record—community nurse and GP version.1.4.1.When patients are discharged from hospital, they will be referred to a community health service center by the in-charge nurse for regular follow-up over 6 months. An “Intervention record—community nurse and GP version” (Additional file 3) will be sent to the community nurse by the in-charge nurse on discharge to record the required postdischarge interventions and outcomes.1.4.2.In order to establish collaboration and maintain communication among the doctor and nurse at the hospital, the patient and the GP and nurse at the community health service center, a two-way referral letter has been developed (Additional file 4).1.4.3.The in-charge nurse at the hospital will contact the GP and nurse in the community health service center through a telephone call and will fill in the two-way referral letter for patients.1.4.4.The in-charge nurse will help patients to contact the nearby community health service center for the follow-up visit. Patients will be advised of the community health service center they have been referred to, and the name and contacts of the GP and nurse in the community health service center.1.4.5.Data in relation to the patient’s demographic information, pharmacotherapy history and other clinical information will be sent to the community nurse by the in-charge nurse on discharge.1.4.6.Patients will take the referral letter and discharge abstract to the community health service center for the follow-up visit.1.5.Monitoring.The in-charge nurse at the hospital will keep track of the patient’s referral progress through making telephone calls with the patients and community nurses to ensure patients are seen at the community health service center.

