
#### Stage 2: regular follow-up interventions over 6 months at community health service centers

2.1.Fortnightly telephone call.Patients will receive a fortnightly telephone call at home from the community nurse to monitor their progress toward setting goals and medication adherence.2.2.Monthly community health service center visit.Patients will be asked to visit the community nurse and GP at the community health service center every month for follow-up visits.2.2.1.Patients will receive blood pressure measurement every month by the community nurse.2.2.2.Patients will receive a review and assessment from the community nurse on their adherence to medication and lifestyle recommendations, and their progress toward lifestyle modification goals.2.2.3.Patients will receive reinforced health education from the community nurse to improve their self-management ability and treatment adherence. Patient will be given health education on preventing or treating geriatric conditions based on the “Fulmer SPICES Comprehensive Assessment Tool for Older Adults”.2.2.4.Patients will receive an assessment from the GP on their clinical outcomes, problems of nonadherence to medication, medication side effects, drug therapy problems, drug-related needs and clinical events occurred.2.2.5.Patients will be asked to discuss their individualized treatment plan and medication adjustment with the GP.2.2.6.Patients will be asked to document their medication changes in the “intervention diary—patient version”.2.2.7.Patients will be reminded of the categories, dosage and frequency of medication required to be taken prior to the next visit by community nurse.2.3.GP and medical specialist collaboration.The GP will discuss with the medical specialist at the hospital via email or telephone when necessary to adjust medication. BP, HbA1c and lipid readings will be recorded by the community nurses and formatted as a monthly report and then sent to medical specialists for review. Urgent symptoms will be communicated to the medical specialist immediately for additional orders by the GP.

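### Adverse events and unplanned admissions are recorded on different forms and with unequal enquiry in the two arms, so both comparisons are open to differential ascertainment

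*Protocol article*

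**What the plan says.** Under Secondary outcomes, outcome (5) is the incidence of adverse events and complications linked to hypertension, diabetes, treatment or geriatric syndromes, "recorded by patients/or carers in the “intervention diary—patient version". Outcome (6), unplanned admissions and emergency care for uncontrolled hypertension, diabetes and geriatric syndromes, names the same diary as its source. No other source is given for either outcome.

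The diary is introduced under Stage 1 of the intervention (item 1.2.1): "Patients will be provided an “intervention diary—patient version” (Additional file 2"). Among the things patients write in it are "medication adherence, adverse events and unplanned hospital admissions/use of emergency care services".

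The Usual care section describes a different record. Of usual-care patients it says: "They will be asked to record the number of adverse events and unplanned hospital admissions/use of emergency care services during 3-month and 6-month follow-up", and it names a usual care table (Additional file 5) for the purpose.

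Scheduled contact differs too. Stage 2 gives the intervention arm monthly visits to the community nurse and GP. At these visits the GP assesses side effects and any clinical events (item 2.2.4). Item 2.1 adds telephone contact: "Patients will receive a fortnightly telephone call at home from the community nurse", with goals and medication adherence as its stated purpose. Geriatric-condition screening appears in Stage 1, and education based on it appears in Stage 2. Usual care has follow-up and outcome measurement at 3 and 6 months.

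**The concern.** A between-arm comparison of event incidence is interpretable only if an event of a given kind has about the same chance of being recorded in either arm. Here the instrument differs by arm, and so does the number of occasions on which patients are asked what has happened to them. The intervention also looks actively for some of the conditions that the outcomes count, since geriatric syndromes are part of both definitions.

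If recording is more complete in the intervention arm, the observed ratio is pushed upward. A real reduction in events could then disappear, or a harmless programme could appear harmful. These two outcomes carry the trial's evidence on safety and on use of care, so the question matters even though the primary outcome, systolic blood pressure, is not touched by it.

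**Working it through.** The plan states no event rate, power or capture rate for outcomes (5) and (6). Its sample size rests on systolic blood pressure, so there is no figure of its own to reproduce here. The check sets the sections side by side and then shows how unequal capture would move a ratio.

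**1. Source by arm**

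| | Intervention | Usual care |
|---|---|---|
| Named in the outcome definition | Diary | Nothing |
| Form described elsewhere | Diary (Stage 1, Additional file 2) | Usual care table (Usual care section, Additional file 5) |
| Who records | Patients or carers | Patients |
| Items | Adverse events; unplanned admissions and emergency use | The number of each of these |

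Read literally, the definition cannot be applied to usual care. Read charitably, the same outcome comes from two instruments. The diary is also compared with the nurse and GP record to assess compliance (Intervention fidelity), which gives a reason to keep it up to date. Nothing similar is described for the table.

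**2. Scheduled enquiry over 6 months**

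- Intervention: 1 visit a month × 6 months = 6 visits, with GP enquiry about side effects and clinical events.
- Usual care: visits at 3 and 6 months = 2.
- Fortnightly calls: 26 weeks / 2 = 13. These are extra contact, but their stated purpose is goals and adherence, so they are not counted as enquiry about events.

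The documented contrast is about 6 against 2.

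**3. Does the intervention raise detection?** The article's Discussion expects it to. It notes that many complications are silent early on, and that continuous care and monthly monitoring allow them, and functional decline, to be found sooner. The limitations paragraph acknowledges patient bias in self-reported questionnaires but not unequal recording of events.

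**4. Effect on a ratio.** Let each arm's capture be the share of true events that is recorded. Then:

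observed ratio = true ratio × (capture in intervention / capture in usual care)

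The documents give no capture rates. The values below are assumptions that show a range.

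| Assumed capture, intervention vs usual care | Factor | Observed if true ratio 1.00 | Observed if true ratio 0.75 |
|---|---|---|---|
| 95% vs 80% | 0.95 / 0.80 = 1.19 | 1.19 | 0.89 |
| 95% vs 60% | 0.95 / 0.60 = 1.58 | 1.58 | 1.19 |

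The true ratio that would be observed as 1.00 is the inverse of the factor: 0.80 / 0.95 = 0.84 and 0.60 / 0.95 = 0.63. Under these assumptions a true reduction of 16% to 37% would be cancelled. With equal capture the factor is 1 and the observed ratio equals the true one.

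**The case against.** The strongest reply is that the two arms have parallel patient records of the same items. The descriptions of the diary and the table name the same two things, adverse events and unplanned admissions or emergency use. Both forms are also listed together in the information pack under Participant recruitment. On this view the only certain defect is a wording mismatch between the Secondary outcomes and Usual care sections. Much of this stands, and it rules out several stronger readings.

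- **Usual-care events are not captured at all.** A reader might infer this from the outcome definition alone. The Usual care section shows that they are recorded.
- **Enquiry is 19 occasions against 2.** Adding 13 calls to 6 visits gives 19, but the calls are not described as asking about events. The supported figure is about 6 against 2.
- **The diary collects causes and the table only counts.** The outcomes are limited by cause and usual care is asked for a number, so this is tempting. But neither form's description mentions cause, and Additional files 2 and 5 are not shown, so their content cannot be compared.
- **Events found by staff or by screening are added to the intervention count.** The outcomes are what patients or carers record. Staff use a separate record, and nothing says that it feeds these outcomes. Staff contact may prompt a diary entry, but that is as far as the text goes.

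It is also fair to say that admissions are likely to be remembered better than minor adverse events, and that the capture rates above are invented for illustration. None of this removes the core. The definition names one arm's instrument, the instruments differ, and active enquiry and geriatric screening are described in one arm only. This is stated in the article, so it does not depend on detail left to a fuller document.

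**Conclusion.** The point holds as a risk of differential ascertainment. It is not a demonstrated bias. The mismatch between the two sections and the unequal enquiry of about 6 against 2 scheduled occasions can be read directly from the article, and confidence in them is high. The direction, over-counting in the intervention arm, is likely but is an inference from the extra enquiry and screening. The size is unknown. The ratio of 1.19 to 1.58 under equal true rates rests wholly on assumed capture of 95% against 60–80%, applied alike to both outcomes, although admissions are probably less affected. The consequence is limited to two secondary outcomes, but they are the ones that would be cited for safety and use of care. The change should be made.

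**What to change.** - Reconcile the Secondary outcomes and Usual care sections so that the definition of outcomes (5) and (6) names a source that exists in both arms.
- Use one identical event form, with date, type and cause of each event, completed with the same questions at the 3- and 6-month assessments in both arms. Questionnaires are already given out at those times in both arms (Data collection), so the form can travel with them. The diary can remain as an intervention tool.
- Where record access allows, check admissions and emergency visits against hospital records, by the same procedure in both arms. The Usual care section already has some record review: "The researcher will record the HbA1c and lipid levels close to the 3-month and 6-month follow-up" from the medical record. It documents access for those values only, so wider access would have to be confirmed.

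It would not help to exclude events found only through the calls or the screening, because a self-recorded entry does not show what prompted it.

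The cost is one shared form, revised outcome wording and modest record review. Two limits should be stated. Records of the four participating hospitals may miss admissions elsewhere. And since recruitment is under way (Trial status), the date of the change should be recorded so that events collected before and after it can be told apart.

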**Methods:**

A cluster randomized controlled trial will randomly allocate 10 wards from four hospitals in Nanchang to either an intervention group (*N* = 5) or a usual care group (*N* = 5). At least 27 participants will be recruited from each ward and the estimated sample size will be 135 patients in each group. The intervention includes individualized self-care education prior to discharge and 6-month follow-up in community health service centers. Health professionals from both hospitals and community health service centers will be resourced to collaborate on the implementation of the postdischarge interventions that reinforce self-care. The primary outcome is systolic blood pressure at 6-month follow-up adjusted for baseline value. Secondary outcomes are self-care knowledge, treatment adherence, HbA1c and lipid levels, quality of life, the incidence of adverse events and the incidence of unplanned hospital readmission at 6-month follow-up adjusted for baseline value. A multilevel mixed-effect linear regression model will be used to compare the changes in health outcomes between the intervention and usual care groups.

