As a chronic disease, hypertension requires life-long medication treatment. Older patients whose memory function decline are more likely to forget taking medications as prescribed and to experience side effects and adverse reactions. Inappropriate medication management can lead to repeat hospital admission. In a study involving 86 patients who were hospitalized, 49% of hospital admissions were due to medical error [11]. Therefore, it is important to prevent medication-related problems. In this study, health professionals at community health service centers will regularly monitor patients’ medication compliance, deal with the side effects of medication and adjust medical therapies to achieve continuity in optimal medication management.

Therapeutic lifestyle changes (TLC) have demonstrated effectiveness in the control of hypertension and improved quality of life among older people [28]. However, a community-based cross-sectional study in Alexandria found that only one in 10 patients can follow the recommended lifestyle modifications such as dietary change, exercise adjustment and weight control [43]. Factors associated with poor self-management include a lack of understanding of the care plan and low confidence and motivation to make healthy choices. Health education can address these barriers by equipping patients with the motivation, self-care skills and knowledge to manage their chronic conditions. Considering the low level of health knowledge among older people, a sustainable and structured follow-up, including regular health education (involving positive behavior changes and medication compliance), and professional health counseling are required for older patients who are discharged. In addition, the monthly monitoring of conditions for older people in community settings can ensure early detection of their functional decline, which prevents hospital readmission. A study in Canada found that hypertension-related hospital admissions of older patients was reduced by 9% during 10 weeks by implementing a community-based education program [42]. Therefore, a sustainable health system is built through promoting service improvements in primary care, such as intensive follow-up to support older patients to maintain their adherence to medical treatment and healthy lifestyle.

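### Secondary outcome (6) counts admissions and emergency visits only for listed causes that omit treatment, so a fall in it need not mean fewer admissions overall

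*Protocol article*

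**What the plan says.** All references are to the protocol article.

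- **Secondary outcomes, item (6):** "the incidence of unplanned hospital admissions/use of emergency care services due to uncontrolled hypertension, diabetes and geriatric syndromes recorded by patients or carers". This is the full definition of the admission outcome, and it carries a list of three causes.
- **Secondary outcomes, item (5):** "the incidence of adverse events and complications associated with hypertension, diabetes, treatments and geriatric syndromes recorded by patients/or carers". This list has four causes, one of which is treatment.
- **Stage 2 of the intervention, items 2.2.4 and 2.2.5:** at monthly visits the GP assesses side effects and drug therapy problems, and the patient discusses the treatment plan and medication changes with the GP. The Usual care section describes outpatient follow-up with outcome measures at 3 and 6 months and no such monthly review.
- **Discussion:** poor handling of medication is named as something that can bring a patient back into hospital, and community staff are to adjust therapy.
- **Recording:** the patient diary (Stage 1, item 1.2.1) has intervention patients note unplanned admissions and emergency care use. For usual care patients the instruction reads: "record the number of adverse events and unplanned hospital admissions/use of emergency care services during 3-month and 6-month follow-up in a usual care table". Neither description limits the events by cause.
- **Blinding and allocation concealment; limitations in the Discussion:** patients learn their allocation after baseline data collection, and the trial is described as open label.

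**The concern.** An outcome restricted by cause is a fair measure of all admissions only if the causes left out are unaffected by the intervention. Here treatment is left out, and the intervention acts on treatment. It could plausibly move treatment-related admissions in either direction: up through more frequent medication changes, or down through closer monitoring, which is what the Discussion hopes for. In both cases outcome (6) as worded need not register the change.

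The restriction also makes the count depend on a judgement about cause. The events are recorded by people who know their group. Patients in the intervention arm have a monthly conversation about side effects, so they may be readier than usual care patients to see an event as drug-related. The same event could then fall outside (6) in one arm and inside it in the other.

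What is at stake is how a lower figure in the intervention arm may be read. The natural reading, that the programme keeps people out of hospital, is not what the outcome measures.

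**Working it through.** The article gives no admission rate, effect size or power for this outcome, so there is no figure to reproduce. The check compares the definitions and then works through what follows from them.

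**1. The two cause lists side by side**

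| Cause | Outcome (5), adverse events | Outcome (6), admissions and emergency care |
|---|---|---|
| Hypertension | yes | only if uncontrolled |
| Diabetes | yes | yes |
| Geriatric syndromes | yes | yes |
| Treatment | yes | not listed |

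The lists differ in two places. Both differences remove from (6) events that could follow from drug treatment and that (5) would count.

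**2. What outcome (6) estimates**

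Assign each event one cause and write, for each arm, A = L + T + U, where

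- A = unplanned admissions or emergency visits for any cause,
- L = those attributed to the three listed causes,
- T = those attributed to treatment and not classed under a listed cause,
- U = all others.

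With Δ for intervention minus usual care, ΔA = ΔL + ΔT + ΔU. Outcome (6) estimates ΔL alone. It equals ΔA only if ΔT + ΔU = 0. There is no particular reason to expect ΔT = 0, because medication review and adjustment are part of what is being tested.

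**3. Direction, with assumed rates**

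None of these rates is in the article. They show the mechanism and are not an estimate. Assume L is 20% in usual care and 14% in the intervention arm, T is 2% in usual care, and ΔU = 0. Then ΔL = 14 − 20 = −6 points throughout.

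| T in intervention arm (assumed) | ΔT (points) | Outcome (6) shows, ΔL | Any-cause difference, ΔL + ΔT |
|---|---|---|---|
| 0% | −2 | −6 | −8 |
| 2% | 0 | −6 | −6 |
| 4% | +2 | −6 | −4 |
| 6% | +4 | −6 | −2 |
| 8% | +6 | −6 | 0 |

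Outcome (6) reads the same in every row. It understates the overall benefit in the first row and overstates it in the last three.

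**4. Attribution**

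Suppose the true L is the same in both arms, and a share q of those events is attributed to treatment instead. The recorded count is then L(1 − q), and the apparent difference is −L(q in intervention − q in usual care). If intervention patients relabel more often, outcome (6) shows a reduction although nothing has changed. In an any-cause count, moving an event from one cause to another leaves the total as it was.

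**The case against.** **Treatment harm is already an outcome.** A drug reaction that leads to admission is an adverse event under outcome (5). This stands. A reader might infer that the trial cannot show harm from its medication component, and the article does not support that. What is missing is narrower: (5) does not show which treatment-related events led to admission.

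**Some treatment-caused admissions can still count under (6).** The Background lists falls among geriatric conditions, a diabetes-drug event may be put down to diabetes, and an admission after missed antihypertensives may well be uncontrolled hypertension. This also stands, so such an admission can drop out of (6) but does not always do so. Where it lands depends on the attribution.

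**The size might seem to be available from the Discussion.** It cites a study of 86 hospitalized patients in which "49% of hospital admissions were due to medical error". A reader might take this as the treatment-related share of admissions. It is not: medical error is not the same as treatment side effects, and the statement does not exclude admissions for hypertension or diabetes.

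**The abstract and the recording forms might seem to contradict the definition.** The abstract's Methods has "the incidence of unplanned hospital readmission at 6-month follow-up adjusted for baseline value" with no cause limit. But an abstract shortens, and recording every event while analysing a subset is consistent. These passages are weak evidence of contradiction. Their use here is to suggest that the any-cause data are already being collected.

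**Who assigns the cause is not stated.** The article says who records the events, and fuller classification rules may exist elsewhere. That is fair. The point rests on self-recording by unblinded people and on the need to attribute a cause at all. An any-cause count would still rely on self-report and on the patient's view of what was unplanned, so it reduces this bias without removing it.

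**Condition-specific admission is a legitimate outcome for this programme.** Agreed, and it should be kept.

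**Conclusion.** The concern holds in a limited form. Followed as written, outcome (6) can show a reduction while admissions attributed to treatment go uncounted, and it depends on causes attributed to events that unblinded patients or carers record. A lower figure in the intervention arm therefore does not by itself show that fewer people were admitted or needed emergency care.

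The conclusion rests on three readings of the text: that the cause list in item (6) is meant literally, that medication adjustment belongs to the intervention, and that the admission records are self-kept in an open-label trial. All three are stated in the article.

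The size of any distortion cannot be derived, because the article gives no admission rates by cause or overall. The distortion could run in either direction. This is a secondary outcome, and the primary comparison of systolic blood pressure is not affected.

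**What to change.** - Analyse unplanned hospital admission or emergency care use **for any cause**, from discharge to 6 months, in both arms. The diary and the usual care table are described as holding these events without a cause limit.
- Keep the present cause-specific count beside it, and add treatment-related admissions as a listed category so that item (6) matches item (5). Show that category separately, so that a shift between causes can be seen.
- State in advance that a reduction in admissions will be concluded only if the any-cause count supports it.

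**Cost.** A short change to the outcome definition and one further analysis. The any-cause count needs no new data if the forms are as the article describes them; the forms themselves are additional files that were not available for this check. The treatment-related category needs a recorded cause, which outcome (6) already requires. The trial is registered and recruiting, so the change should be dated, entered in the registry record and made before outcomes are compared by group. The downside is small: unrelated admissions dilute the any-cause signal in a trial of 270 participants, and the cause-specific result is retained for that reason.
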